**K. Personnel who will conduct the study, including:**

1. Indicate, by title, who will be present during study procedure(s): PI, Co-I, study coordinator, research technician, and GRAs.
2. Primary responsibility for the following activities, for example:
  - a. Determining eligibility: [name], study coordinator with assistance from PI ([name]).
  - b. Obtaining informed consent: PI ([name]) and [name]
  - c. Providing on-going information to the study sponsor and the IRB: PI ([name]), study coordinator
  - d. Maintaining participant's research records: study team
  - e. Completing physical examination: GRAs
  - f. Taking vital signs, height, weight: GRAs
  - g. Drawing / collecting laboratory specimens: Landon Center on Aging
  - h. Performing / conducting tests, procedures, interventions, questionnaires: [name] and GRAs.
  - i. Completing study data forms: study team
  - j. Managing study database: study coordinator and PI ([name])

**L. Assessment of Subject Safety and Development of a Data and Safety Monitoring Plan**

- a. Given that the proposed investigation utilizes a randomized controlled trial study design, we will have an independent Data and Safety Monitoring Board (DSMB) for the trial. The primary responsibility of the board will be to protect the safety of the research participants and ensure adherence to human subject protection policies. Secondary responsibilities will be related to the quality and validity of research protocols and data quality. The DSMB will be identified prior to the start of the research project. The members of the DSMB will likely include experts in multiple sclerosis research, exercise, medicine, biostatistics, and ethics. The Data and Safety Monitoring Board (DSMB) will include at least three people who are independent of the trial and have one or more of the following qualifications: physicians or researchers with experience in clinical trials related to frailty or exercise in people with multiple sclerosis. The DSMB members will elect a Chairperson and a Safety Officer (SO). The Chairperson and the SO may be the same person. Once the members of the DSMB have been identified, the Institutional Review Board will be notified of the membership of the DSMB and its specific responsibilities. The report of the DSMB will follow the template of the National Institutes of Health: protocol synopsis, study timetable, action items from prior DSMB meetings, protocol changes, enrollment (actual versus expected), screen failures, protocol deviations, demography, baseline characteristics, treatment duration, adverse events, and serious adverse events. We propose that the DSMB have one in-person meeting and one mid-year teleconference during years 1-2. Other meetings will be convened at the request

of the committee. The members of the DSMB will also receive regular data reports at a schedule agreed upon by the members. Types of analyses to be performed: Analysis of completion, accuracy, and correct and timely response to events, data quality, protocol-adherence and attrition. Safety-related triggers that would cause the PI to stop or alter the study: unanticipated serious adverse outcome to participant. The major tasks of the DSMB will be to (1) assess whether there are safety findings that require stopping or modifying the study and (2) adjudicate Serious Adverse Events and deaths that are unexpected and/or atypical for healthy young-old adults. The DSMB will receive un-blinded safety data quarterly. If the DSMB detects safety concerns, then the DSMB may request safety data more frequently. If, at any time during the study, the perceived risk/benefit of treatment changes, the DSMB has the authority to recommend protocol modification or study curtailment. During the course of the trial, the DSMB will receive information from concomitant trials performed or published elsewhere. In addition, the DSMB will receive periodic reports about recruitment and safety information. Based on information received during the trial, the DSMB may choose to recommend changes to the protocol. If protocol changes are necessary, the implementation of changes will avoid unmasking the accumulated outcomes to the clinical trial personnel who are responsible for the ongoing performance of the trial. If there are unforeseen safety hazards that emerge during the clinical trial, then the Data and Safety Monitoring Board will have the authority to recommend temporary or permanent cessation of the trial.

- b. Furthermore, the Principal Investigator (PI) will be responsible for ensuring participants' safety on a daily basis. Trained research personnel will perform monitoring weekly to assess for data entry errors, outliers, and missing data. Personnel will also perform audits quarterly to assess adherence to the protocol, informed consent documents, source documents, regulatory documents, signature lists, site delegation authority lists, screening lists and enrollment logs. The appointed study monitor will sign the monitor log and submit a monitor report to the PI. The research personnel will use multiple techniques to minimize missing data, losses to follow up, and non-response bias. In summary, the investigators will ask participants to provide primary and back-up contact information. In addition, the protocol permits assessment of outcomes telephone survey, and postal survey if the participant declines a face-to-face visit. The investigators will create Standard Operating Procedures for electronic data entry, data access, data back-up, and data security.
2. The investigators will use the definitions for "Adverse Event" and "Serious Adverse Event" as defined by the International Council for Harmonization. Data from the study will be monitored on a continuous basis by the PI, and co-investigators. All serious adverse events (SAEs), adverse events (AEs), will be reviewed by the PI on an ongoing basis. Participants will be encouraged to report any discomfort or adverse outcomes they experience during each study visit. Trained research assistants will record any AE/SAE during the intervention. The study team will report SAEs and AEs to the PI as soon as possible.
3. Research personnel will ascertain adverse events from the participant by non-directive questions during the research visits. In addition, participants may voluntarily report

adverse events. Research personnel will record adverse events on the case report form. The investigators will score the adverse event in terms of:

Severity: mild, moderate, or severe.

Clinically significant: yes or no.

Requires therapy: yes or no.

Relationship to the experimental interventions: suspected or not suspected.

Duration of the adverse event: start date, end date, or ongoing at visit.

Serious adverse event: yes or no.

When research personnel learn that a participant has experienced an adverse event, research personnel will contact the PI on the same day to receive instructions for the transfer of the participant for treatment and follow-up of the adverse event. In addition, research personnel will complete an adverse event form. Participants with adverse events are eligible to remain in the trial unless there is withdrawal of consent. Participants who have experienced a serious adverse event will be withdrawn from the study.

The investigator will communicate with the participant and primary care physician (if deemed necessary by PI) to acquire information to complete the treatment questions on the adverse event form. The specific questions are: no action taken (i.e., further observation only); intervention temporarily interrupted; intervention permanently discontinued due to this adverse event; patient hospitalized. The investigator will continue to communicate with the participant and primary care physician until resolution to record change of severity, change of suspected attribution to intervention, and change of treatments for the adverse event.

The investigators and the Data and Safety Monitoring Board will review Adverse Events and Serious Adverse Events. If unexpected experimental-related adverse events emerge during the course of the trial, then the investigator will report the adverse events to the Institutional Review Board and the National Institutes of Health within the timelines required by each entity.

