## **II. Research Plan and Design**

**A. Study Objectives:** The broad research goal of this study is to provide novel data regarding the potential efficacy of multimodal exercise to reduce frailty in pwMS and will set the foundation for our long-term goal of identifying novel interventions to improve the quality of life of persons with MS. The specific aims of the project will be to determine the feasibility of a multimodal exercise training in pwMS (Aim 1), and to explore the effects of the multimodal exercise training on frailty in pwMS (Aim 2).

**B. Study Type and Design:** Using a pilot single-blind randomized controlled trial (RCT) study design, ambulatory individuals living with MS will be allocated to 6 weeks of multimodal exercise training (n=30) or to a waitlist control group (n=30) (Figure 1).

[figure not shown]

Figure 1. Study design.

The following outcomes will be collected to accomplish the study aims:

**Aim 1: Feasibility Outcomes:** The following outcomes, based on the guiding principles for feasibility studies, will be utilized to examine the feasibility of the Virtual Reality and Resistance Training for MS (VRRT4MS) program in the study population: a) participant recruitment, i.e., number of consented individuals/number of approached individuals (expressed as a percentage); b) retention rate, i.e., number of participants completing the intervention/number of participants enrolled at baseline (expressed as percentage); c) appropriateness of data collection and training procedures, as quantified through the percentage of missing data for analysis purposes (i.e., missing items in the frailty index) and through time spent in training, respectively; d) participant safety, i.e., number of adverse and serious adverse outcomes throughout the study and self-reported pain, assessed by the numeric pain rating scale, during each training session (the Borg and Omni scales of perceived exertion will also be administered throughout each training session to differentiate exertion from pain); e) evaluation of resources, i.e., difference between proposed and actual research timeline; f) user engagement, i.e., study participant feedback questionnaire. We note that the effects of VRRT4MS on the primary frailty outcome, namely the frailty index (AIM 2), will also represent a further feasibility outcome of the intervention.

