| Biomarkers                     | 12            | Laboratory tests                                  | NfL, BDNF, GFAP, CRP, IL-6, IL-10, TNF-alpha, IFN-gamma, and CXCL9, mi-RNAs.                                                                                                  |

**Legend:** ADL: activities of daily living, MSQoL-54: 54-item multiple sclerosis quality of life questionnaire, MFIS: modified fatigue impact scale, CVLT-II: California verbal

learning test, SDMT: symbol digit modalities test, BVMT: brief visuospatial memory test; TMT: trail making test, 6MWT: 6-minute walk test, BP: blood pressure, BMI: body mass index, CRP: c-reactive protein.

All study outcomes will be assessed in a standardized manner during Visit 2 and 3. Following visit 2, participants will be randomized to one of the two groups based on pre-generated randomization codes prepared by the biostatistician. In accordance with the CONSORT guidelines, sequence generation, allocation concealment and group allocation will be blinded and separate processes. Participants will then either complete the waitlist period (passive control) or attend the exercise training visits 3 times a week, for 6 weeks, totaling 18 training visits. Each training visit will last one hour. The training visits will take place at the Laboratory for Advanced Rehabilitation Research in Simulation at the University of Kansas Medical Center.

**Intervention (Multimodal exercise) Group:** Participants will complete 15 minutes of virtual reality treadmill training (VRTT), followed by 30 minutes of progressive evidence-based resistance training (RT), followed by other 15 minutes of VRTT. This interval training design was chosen to induce acute fatigue before the last bout of VRTT. See Table 2.

**Table 2.** The Multimodal exercise program.

| Exercise components      | Duration   | Description                                                                                                                    | Target (frailty domains)*             |
|--------------------------|------------|--------------------------------------------------------------------------------------------------------------------------------|---------------------------------------|
| 1) VR treadmill training | 15 minutes | Treadmill walking with interactive virtual environment.                                                                        | - Slowness
- Cognition             |

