| 2) RT                    | 30 minutes | Seated leg press, seated hamstring curls, seated calf raises, seated chest press, seated lat-pulldowns, seated shoulder press. | - Muscle weakness
- Shrinkage      |
| 3) VR treadmill training | 15 minutes | Treadmill walking with interactive virtual environment.                                                                        | - Slowness, Cognition
- Exhaustion |

**Legend:** VR: virtual reality, RT: resistance training, \* The multimodal exercise program will also inherently target the 'inactivity' component of frailty.

Both the VR and RT components of the program will be individualized based on the participant's abilities and the training progression will be adjusted every 2 weeks. Over-ground gait speed will be assessed prior to the intervention and every two weeks thereafter and will be utilized to set the treadmill speed for the VR component. As part of VR, participants will navigate through a virtual environment projected on a TV screen while receiving feedback from the system (Figure 2). The RT component will consist of performing evidence-based RT exercises, as fully described in Table 2. In the event participants are unable to complete 15 minutes of continuous walking, walking duration will be progressively increased in 1–3-minute bouts until the prescribed time is reached. The estimated 1-repetition maximum (1-RM) of all RT exercises will be evaluated using validated standard procedures (for untrained individuals) prior to the intervention. At the beginning of the intervention, participants will complete 3 sets of 8-12 repetitions at 20-30% of the 1RM and slowly progress up to 80% over the course of 8 weeks. The end point of each set will always be limited to volitional fatigue. Recovery periods of 2-4 minutes will be prescribed between sets and exercises.

**Control Group:** Participants randomized to the control group will be put on a waitlist (passive control group) for 6 weeks. Upon completion of Visit 3, participants in the control group will be able to receive the intervention, if they wish so.

[figure not shown]

Panel A

[figure not shown]

Panel B

Figure 2. Gait Better (TM) virtual reality (VR) treadmill training set up. Panel A. Camera detects markers on feet and projects them on screen. Panel B. View of VR monitor depicting individual's virtual feet, visual distractors, and obstacles.

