#### F. Risk/benefit assessment:

1. **Physical risk:** The main risk of this study would be risks typically associated with exercise. Participants may experience shortness of breath, muscle soreness, dizziness, and increased heart rate. These effects typically resolve shortly after the exercise is stopped, however, muscle soreness may last a few days. Given the prevalence of fatigue in persons with MS, it is possible that participants will become fatigued during study visits. Additionally, the blood draw may present a risk to participants. Participants may experience momentary discomfort and bruising. Infection, excess bleeding, clotting and fainting are also possible although their occurrence is unlikely. Participants may also be at risk of falling during the exercise training. Injuries sustained from falling could range from mild, such as scratches and bruises, to severe, such as head injuries and/or bone fracture. There is also the risk of a data breach or unintentional disclosure, which is a risk to a participant in ANY research study. There is a risk of contracting COVID-19, which is also present in any research which involves face-to-face interaction between humans. Finally, the pressure pain threshold test may be uncomfortable for some individuals.

The first risk identified was the risk of incurring symptoms typically experienced during exercise. This risk will be mitigated in a variety of ways. Participants will be allowed breaks whenever they need it and be given access to water. Participants will only be

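### Adverse events are asked about only at research visits (19 after randomization for exercisers, one for the waitlist), so whole-study counts of non-serious events are not comparable between arms

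*Protocol*

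**What the plan says.** Protocol section II.L ties active ascertainment to visits: "Research personnel will ascertain adverse events from the participant by non-directive questions during the research visits". The other statements there follow the same pattern. Encouragement to report is linked to visits ("Participants will be encouraged to report any discomfort or adverse outcomes they experience during each study visit"), and staff recording is linked to training ("Trained research assistants will record any AE/SAE during the intervention"). The only route that does not depend on a visit is spontaneous: "In addition, participants may voluntarily report" events. Events already known are followed until they resolve.

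The visit schedule in section II.E differs sharply by arm. Randomization follows Visit 2. Exercisers then "attend the exercise training visits 3 times a week, for 6 weeks, totaling 18 training visits". For the others, "Participants randomized to the control group will be put on a waitlist (passive control group) for 6 weeks". Both arms return for Visit 3. No interim call or diary is described for the waitlist. The telephone and postal option in section II.L is for outcome assessment when a participant declines a face-to-face visit; it is not a scheduled safety contact.

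The safety outcome under Aim 1 (section II.B) is the "number of adverse and serious adverse outcomes throughout the study", together with pain ratings at training sessions. Section II.L has the safety board receive unblinded safety data every quarter.

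**The concern.** Falls, fatigue, pain and relapse can be expected in frail people with MS whether or not they train. If one arm is asked every two or three days and the other once after six weeks, more of these events will be found in the first arm at the same true rate. An apparent excess under exercise could then be an artefact. A real excess could equally be dismissed as one.

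Analysis cannot repair this later, because events that nobody asked about are not in the data. The counts matter in two places: the feasibility report, which is meant to inform a larger trial, and the safety board's unblinded review, where members are likely to set the arms side by side whether or not a test is planned.

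**Working it through.** **Schedule (section II.E).** Training visits: 3 per week × 6 weeks = 18, as the Protocol states. The payment ceiling in section III.G agrees: 2 × $50 + 18 × $5 = $190.

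**Scheduled contacts after randomization, up to and including Visit 3.** Training visits are read as research visits.

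| | Exercise | Waitlist |
|---|---|---|
| Training visits | 18 | 0 |
| Visit 3 | 1 | 1 |
| Total per participant | 19 | 1 |
| Total for 30 per arm | 570 | 30 |
| Total for 24 completers per arm | 456 | 24 |
| Mean recall interval over 42 days | 42/19 = 2.2 days | 42 days |

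This count rests on the six-week programme. Section II.E also describes the resistance progression as running over 8 weeks; the two statements must be reconciled.

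**Size of the artefact, simple form.** Assume equal true event rates, 90% of events captured with two-to-three-day recall, and 30 to 70% with six-week recall. None of these figures is in the Protocol. The observed exercise-to-waitlist ratio is then

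- 0.90/0.70 = 1.29 at best
- 0.90/0.30 = 3.00 at worst

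**Size of the artefact, second form.** Assume recall decays exponentially with half-life h, so k = ln 2/h. With t days between contacts, the captured fraction is (1 − exp(−kt))/(kt). Using t = 2.2 and t = 42:

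| Assumed h (days) | Exercise | Waitlist | Ratio |
|---|---|---|---|
| 7 | 0.90 | 0.24 | 3.8 |
| 14 | 0.95 | 0.42 | 2.3 |
| 28 | 0.97 | 0.62 | 1.6 |
| 56 | 0.99 | 0.78 | 1.3 |

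Both forms ignore spontaneous reports, which would narrow the gap, and neither separates serious from non-serious events. They agree on direction and rough size.

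**Same questions on the same schedule.** The captured fraction is then equal in both arms and the spurious ratio is 1.0 under this model, whatever the half-life. With weekly questions to both arms, for example, it would be 0.72, 0.85, 0.92 and 0.96 for the four half-lives above.

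**The case against.** The strongest reply is that the Protocol plans no between-arm safety comparison. Safety is listed as a feasibility measure of the training programme. The stated expectation concerns serious events during training sessions, which waitlist recall cannot touch. The only between-group test named is the Wilcoxon test on change in frailty index. The named trigger for stopping or altering the study is an unanticipated serious event, and each event is scored for severity, seriousness and suspected relationship. The board can also take the visit schedule into account. All of this stands, and it confines the problem to descriptive by-arm counts, mainly of non-serious events. It does not make those counts comparable.

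Some background problems are also measured alike in both arms: fall history and fatigue at Visits 2 and 3, and pain questionnaires at screening and Visit 3. These give a partial cross-check. They are not adverse event records, and relapse is not among them.

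Unequal contact is inherent in a passive waitlist, so regular calls to controls are a design option and not the correction of an error. That also stands. The core remedy therefore uses a visit that both arms already attend.

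A reader might further infer that nothing is asked after the last blood draw. The documents do not support that. At Visit 2 the test battery of about 90 minutes follows the draw, and Visit 3 repeats those procedures, so questions can still be put that day. Controls who take up training have further visits. What remains is narrower: no scheduled contact after Visit 3 is described for exercisers or for controls who decline training. Delayed effects of that visit then rest on spontaneous reports. Section II.F itself rates the relevant risks as remote: "Infection, excess bleeding, clotting and fainting are also possible although their occurrence is unlikely".

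**Conclusion.** The concern holds in a limited form. The 19-to-1 difference in scheduled contacts follows directly from the Protocol. Carried out as written, the plan yields whole-study counts of non-serious events that are not comparable between arms and would tend to show an excess under exercise with no true effect.

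The size is unknown. A ratio of about 1.3 to 3 follows from the assumed capture rates, and up to 3.8 from the shortest recall half-life tried. These are illustrations, not estimates for this trial.

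It would be tempting to conclude that the trial's safety hypothesis fails or that the board's oversight is unsound. Neither follows. The hypothesis about serious events in training sessions is unaffected, serious events are less likely to be forgotten, and voluntary reporting is open to both arms. This is an inexpensive improvement worth making before enrolment, not a fundamental defect.

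**What to change.** At Visit 3, once the blinded assessments are finished, have an existing team member other than the blinded assessor ask both arms the same adverse event questions covering the whole period since randomization. The order and the choice of person matter because an account of training-related events would reveal the allocation.

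Base any by-arm display or comparison, including the safety board's tables, on this common source only. Tabulate events found at training sessions separately, as safety data on the exercise arm. Recording and reporting of individual events from any source stay as they are.

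To cover delayed effects of Visit 3, make one brief call to both arms a few days afterwards. Do not attach this to the return of the wearable sensor, because the Protocol does not say how or when the sensor comes back.

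The cost is one form, a few minutes at an existing visit and one short call per participant. There are two downsides. Counts from the common source will be lower than counts from all sources. Recall over six weeks also remains imperfect in both arms. Identical calls to both arms during the six weeks, for example every two weeks (about three per participant), would shorten recall, but they are optional.

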**V. Data Analysis and Reporting**

**A. Statistical and Data Analysis:** Descriptive statistics (frequency/percent and mean/SD) will be mainly used to summarize participants' characteristics and intervention outcomes. The means and 95% CIs for pre-post changes in the primary (i.e., frailty index) outcome will be estimated. No imputation will be considered for missing data. The Wilcoxon rank sum test will be used for comparing the pre-post changes in frailty index between the two groups.

- B. Outcome:** The intervention will be considered feasible if the retention rate and the proportion of completed sessions are more than 80%. We expect that at least 80% of participants will complete the multimodal exercise training and that no serious adverse events will be recorded during the training sessions. We expect that participants in the experimental group will have greater reduction in frailty index than participants in the control group. Finally, we expect that participants randomized to multimodal exercise will also exhibit a clinically meaningful change in the frailty index.
- C. Study results to participants:** A short, written letter of the study results will be sent to participants once the study has concluded.
- D. Publication Plan:** Findings from this study will be presented at scientific conferences and published in research journals.

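### A serious adverse event ends study participation, not only training, so a participant able to attend Visit 3 is by implication lost to the frailty-index comparison

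*Protocol*

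**What the plan says.** Protocol II.L, item 3, states: "Participants who have experienced a serious adverse event will be withdrawn from the study". The sentence just before it treats other events differently: "Participants with adverse events are eligible to remain in the trial unless there is withdrawal of consent". The adverse event form in the same item has its own category for stopping training, "intervention permanently discontinued due to this adverse event", next to a category for temporary interruption.

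On outcomes, II.E.2 says: "All study outcomes will be assessed in a standardized manner during Visit 2 and 3". Visit 2 is baseline, so Visit 3 is the only later frailty-index measurement. Sections II.C.1 and V.A compare pre-post changes between groups by the Wilcoxon rank sum test, and V.A adds: "No imputation will be considered for missing data".

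On follow-up, II.L.1.b says: "The research personnel will use multiple techniques to minimize missing data, losses to follow up, and non-response bias". It also says that "the protocol permits assessment of outcomes telephone survey, and postal survey if the participant declines a face-to-face visit".

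On feasibility, II.B defines retention as "number of participants completing the intervention/number of participants enrolled at baseline", and II.C.1 requires it to exceed 80%. The general withdrawal criteria in II.D.3 are discretionary, but they too concern leaving the study and say nothing about Visit 3.

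**The concern.** Stopping training after a serious event is a clinical decision. Ending outcome assessment is a separate one, and the rule merges the two. It applies to a waitlist participant, who has no training to stop, and to an unrelated event that has resolved.

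Two things are at stake. First, the Aim 2 comparison needs both visits, so a participant without Visit 3 contributes nothing to it. The reason for the loss is a health event, which may well be related to frailty. Second, a participant whose training could have been interrupted and resumed is instead made a non-completer, which lowers the retention rate used for the feasibility decision.

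**Working it through.** **Does the loss follow from the text?**

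- Withdrawal is mandatory and is from the study. The wording cannot mean training only, because the same item lists stopping the intervention separately and the rule also covers the waitlist arm.
- Contact after the event (II.L, item 3) serves to follow the event to its resolution. No outcome assessment is mentioned.
- The telephone and postal option is worded for someone who declines a visit. It also could not supply the whole index: in Table 1, physical performance (6 items) and biomarkers (12 items) alone make up 18/70 = 26% of the items.
- A missing Visit 3 means no change score, and no imputation replaces it.

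The loss is thus an implication of the rule and of the lack of any assessment after withdrawal. No sentence cancels Visit 3 outright.

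**The plan's own figure.** II.C.3 gives 30 per group, 15% dropout and at least 24 completers. 30 × (1 − 0.15) = 25.5, which agrees.

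**How many participants?** II.F.1 reports no serious events in 108 people in the earlier treadmill intervention. The one-sided 95% upper bound is 1 − 0.05^(1/108) = 2.74%.

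- Expected at that rate: 30 × 0.0274 = 0.82 per arm and 60 × 0.0274 = 1.64 in all.
- P(at least 1 of 30) = 1 − (1 − 0.0274)^30 = 0.56. P(at least 2 of 30) = 0.20.
- Able to attend Visit 3, if 25%, 50% or 100% could (assumed): 0.21, 0.41 or 0.82 per arm.

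Because that rate may not carry over, the table shows other assumed rates. Withdrawals are added on top of the 15% dropout, so completers = 25.5 × (1 − rate).

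| Assumed rate | Withdrawn of 60 | Completers per arm |
|---|---|---|
| 2% | 1.2 | 25.0 |
| 5% | 3.0 | 24.2 |
| 10% | 6.0 | 23.0 |

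Only the 10% case falls below the planned 24.

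**How much bias?** Suppose one participant's change is worse than the others' mean by g. The full arm mean is then higher (worse) by g/n, and removing that participant makes the arm look better by g/n. With g assumed to be 0.03 to 0.06:

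| g | n | Shift g/n | Share of the 0.03 threshold |
|---|---|---|---|
| 0.03 | 30 | 0.0010 | 3.3% |
| 0.06 | 30 | 0.0020 | 6.7% |
| 0.03 | 24 | 0.00125 | 4.2% |
| 0.06 | 24 | 0.0025 | 8.3% |

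Equal losses of similar participants in both arms give a net shift of about zero. In a simulation under no treatment effect (20,000 runs per setting, n = 24 or 30, assumed SD of change 0.04 or 0.06, one worse participant per arm and the one in a single arm removed), the Wilcoxon type I error stayed close to 0.05 (0.046 to 0.052).

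**Retention.** Taking the exercise arm of 30 as denominator (the protocol does not say which it uses), 25/30 = 83.3% passes and 24/30 = 80.0% does not. Near the threshold, one participant barred from resuming training can decide the result. For someone who stops training for good, retention is the same with or without Visit 3.

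**The case against.** The strongest reply is that nothing material follows. This is a convenience-sample pilot, analysed mainly by description, with 15% dropout already expected (30 × 0.15 = 4.5 per arm). A fraction of one participant disappears within that allowance. This stands, and it sets the low priority.

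A second reply is safety. Participants are frail, and Visit 3 includes fasting, a blood draw, walking and strength tests and pressure-pain testing. A firm exit after a serious event is a defensible precaution. What stands is that Visit 3 must be omitted when it is unsafe. That does not require barring those for whom it is safe.

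A third is that the follow-up measures in II.L.1.b address non-response and loss of contact, so they do not contradict a safety withdrawal. This is fair. The rule works against the stated aim of limiting missing data, but the two are not in formal conflict.

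A fourth is that using data after such an event is a choice of estimand for the SAP. The analysis choice is, but an SAP cannot recover a measurement that was never taken.

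A reader might infer more than the documents support:

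- *That the protocol expressly cancels Visit 3.* It does not; the loss is inferred from silence on assessment after withdrawal.
- *That 0 of 108 caps the event rate here.* That intervention had no resistance training. The treadmill trial described in I.B.3, apparently the same one, did not select for frailty.
- *That the comparison will be biased towards exercise.* Events are sought at research visits, and the exercise arm has 18 training visits against none for the waitlist arm, so earlier detection in the exercise arm is plausible. Nothing in the documents shows its size, or that losses would in fact differ.

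**Conclusion.** The point holds as a low-priority design improvement. Followed as written, the rule removes participants who could still be measured from the Aim 2 comparison, for a health-related reason, and makes non-retained anyone who could have resumed training.

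The expected size is small: about 0.8 participants per arm at the illustrative 2.7% rate, of whom perhaps 0.2 to 0.8 could attend Visit 3, and a shift of 0.001 to 0.0025 per net one-arm loss. These figures rest on assumed attendance, an assumed gap of 0.03 to 0.06 and a rate from a different population and intervention. Type I error is not a concern in the settings examined, and an imbalance between arms is possible but not shown. What is firm is the wording of the rule, the single post-baseline measurement and the lack of any assessment after withdrawal.

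**What to change.** In II.L, item 3, replace the withdrawal sentence with: *After a serious adverse event, training is interrupted or discontinued where clinically needed; Visit 3 is still offered unless consent is withdrawn or the visit is judged unsafe, and the participant's data are kept in the allocated arm.*

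In II.D.3, add: *Participants withdrawn by the investigators are likewise offered Visit 3 unless consent is withdrawn or the visit is judged unsafe.* Without this second sentence, the same participant could be withdrawn under the discretionary criteria and lose Visit 3 in the same way.

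The cost is two sentences and a few extra Visit 3 assessments, some of them partial. Sample size and the planned test do not change, and no safety protection is given up.
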